#### Primary Outcomes

##### Pregnancy Complications

Pregnancy monitoring using the mobile REST mobile app can prevent complications during a mother’s pregnancy compared to not using the app. Once the trial began, the definition of primary results was refined from “pregnancy complications” to “specific conditions of complications experienced by the mother during pregnancy, such as anemia, hypertension, and chronic energy deficiency.” These changes were made before data analysis and have been documented in the protocol.

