Assessment of the results of the research will begin from the implementation of the first class of pregnant women. The total number of meetings was 3. The final result (a comparison of the expected outcome) was at the time of delivery. The research was carried out after ethical approval was obtained. The research locations are in 11 subdistricts in Purworejo Regency (Central Java, Indonesia): Loano, Purwodadi, Bruno, Butuh, Purworejo, Bagelen, Kaligesing, Kemiri, Kutoarjo, Ngombol, and Pituruh. These 11 subdistricts were chosen because they have health centers with inpatient services that make it easier for pregnant women to give birth in their areas.

Each ANC class group consisted of 10 pregnant women and 1 midwife. In each of the 3 meetings, an examination based on the 10T pregnancy examination standard was conducted, which included measuring the weight and height (T1), blood pressure (T2), mid-upper arm circumference (T3), uterine fundal height (T4), tetanus immunization (T5), iron supplement tablets (T6), fetal presentation and fetal heart rate (T7), counseling (including childbirth and postpartum preparation; T8), hemoglobin levels (T9), and care as needed (T10), as per the policy of the Indonesian Ministry of Health [5]. The results of the examination at each meeting were entered into the REST (Risk Identification, Evaluation Counseling, Systematic Monitoring, Troubleshooting) mobile app, and the pregnant women could see these results. If they performed a self-examination outside the ANC class schedule, they could fill in the results of the examination according to what they knew. Midwives and pregnant women were provided with training and a guidebook module for using the app. The control group carried out the standard ANC class without the use of the app, and they were exempt from recording examination results.

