### Randomization, Allocation, and Blinding

Sample determination was carried out using a cluster sampling approach. The target population was all inpatient health centers spread across 11 subdistricts in Purworejo Regency. Based on data from the Health Office, 14 inpatient health centers met the inclusion criteria. Of these, 11 (78.6%) were randomly selected, each representing 1 subdistrict. These 11 subdistricts consisting of 22 pregnant class clusters (C1-C22) were randomized into an intervention group (n=11, 50%) and a control group (n=11, 50%) using the compute-generated random allocation method. A list of cluster codes was entered, and a random sequence was used to divide the groups in order. The results of randomization determined that the first 11 clusters in the list were allocated to the intervention group (C1-C11), while the remaining 11 clusters were allocated to the control group (C12-C22). Randomization was carried out by independent researchers to ensure unbiased random allocation.

The group allocation was kept secret until the intervention group received treatment. Blinding was not possible both for the treatment provider (researcher) and for the sample because the monitoring intervention allowed for active interaction between treatment provider and sample. To ensure the accuracy and completeness of the report, this study adheres to the standards set out in CONSORT (Consolidated Standards of Reporting Trials) EHEALTH V1.6 checklist (Multimedia Appendix 1), which includes a detailed description of the digital intervention and research methodology [23]. The timeline of participant participation was developed in accordance with the SPIRIT (Standard Protocol Items: Recommendations for Interventional Trials) statement (Table 2 and Multimedia Appendix 2) [24].

**Table 2 table2:** SPIRIT^a^ checklist–recommended schedule for study participation.

Study period and activities		Enrollment time point	Allocation time point	Postallocation time points				Close-out time point
		Week 1	Week 0	Month 1	Month 2	Month 3	After month 3	

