**Figure 3 figure3:**
[figure not shown]
Image of the REST mobile app's profile screen. Pregnant women (participants) can monitor their pregnancy based on the results of the examination that have been input by the facilitator midwife and can also fill in the results of the examination carried out outside the implementation of the ANC class. ANC: antenatal care; REST: Risk Identification, Evaluation Counseling, Systematic Monitoring, Troubleshooting.

The fidelity of the intervention was assessed through a variety of strategies. First, the REST mobile app included an internal analytics system that automatically recorded user activities, such as examination results filled in by midwives and the completion of scheduled tasks by pregnant women (recording data on ANC visits). Second, the research assistant conducted periodic monitoring during ANC classes using a standard checklist to observe whether midwives and pregnant women were using the app according to protocol. Third, participants filled in the part of the delivery results they reported themselves. Any deviations from their intended use were documented and analyzed. This combined method allowed us to evaluate the compliance and quality of application usage across the cluster. The REST mobile app includes a built-in troubleshooting and decision support feature designed to assist midwives in early identification and management of maternal health issues. This feature operates on a rule-based algorithm that evaluates input data, such as blood pressure and hemoglobin levels against reference thresholds established by the Indonesian Ministry of Health and WHO guidelines. If an abnormal value is entered, the app automatically flags the entry and provides a visual alert. It then offers a set of recommended clinical actions, such as counseling, closer follow-up, or referral to a higher-level facility. Midwives retain clinical autonomy in making final decisions, but the app serves as a structured guide to enhance consistency and responsiveness in care. This feature was designed to strengthen early detection and ensure standardization in ANC service delivery, particularly in remote or resource-limited settings.

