### Data Management

The data collected will be kept confidential for the duration of the study and disposed of after a period of 5 years. The data collection process from the beginning to the end of the study used 2 different methods. In the control group, data were collected using a form that was transcribed into electronic format, and in the intervention group, data were collected using an app and transcribed into electronic format that was stored on a desktop computer. These stored data will be used for further analysis. The individual appointed as the chair of the student project committee at the institute is responsible for overseeing data management.

To address missing or incomplete data, the researchers implemented proactive data validation and monitoring procedures within the REST mobile app. Real-time data entry validation rules were embedded in the app to minimize input errors and prevent incomplete submissions. In cases where data were missing or inconsistencies were detected, follow-up verification was conducted by the research team through direct contact with the respective participants or midwives, as appropriate. For statistical analysis, missing data will be assessed for patterns and mechanisms. Depending on the extent and nature of the missing data, appropriate methods, such as multiple imputation or complete-case analysis, will be used. To ensure overall data quality and accuracy, regular data audits will be performed, and all electronic data will be stored in secure, access-controlled databases with audit trails. These procedures have been designed to enhance data integrity and minimize bias due to incomplete or inaccurate information.

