## Results

In July 2023, the REST mobile app was prepared and tested in small community groups, including midwives and pregnant women, through simulation. In September 2023, the app was further developed and refined based on the feedback from these small group trials and then introduced to study participants. A total of 22 ANC class clusters were involved, comprising 22 midwives and 220 pregnant women in Purworejo Regency. These were divided into 2 groups: 11 (50%) intervention clusters using the REST mobile app and 11 (50%) control clusters. The majority of participating pregnant women were aged 20-35 years (n=168, 76.4%), consistent with national demographic trends. Approximately 185 (84.1%) had secondary education (junior and senior high school), and 57 (25.9%) had tertiary education (college graduates). The participants were evenly distributed across economic quintiles, reflecting diverse socioeconomic backgrounds, and most lived approximately 1 km from a health facility.

To provide a clearer overview of both completed and planned study phases, Table 4 presents the planned timeline for each phase of the RCT.

**Table 4 table4:** Planned timeline^a^ for study phases.

Phase	Start	End
Ethical approval	April 2023	April 2024
Staff training/preparation	July 2023	October 2023
Participant recruitment	November 2023	January 2024
Intervention implementation	February 2024	July 2024
Follow-up/data collection	August 2024	February 2025
Data analysis	March 2025	June 2025
Report writing/publication	July 2025	December 2025

^a^Dates are tentative and may be adjusted based on field conditions and recruitment outcomes.

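### A primary outcome was redefined after the trial began, on an undated and still open list, and the assurance that this preceded analysis does not rule out a choice made with outcomes known

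*Protocol article*

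**What the plan says.** Under Primary Outcomes, Pregnancy Complications, the article reports: "Once the trial began, the definition of primary results was refined from" pregnancy complications in general to "specific conditions of complications experienced by the mother during pregnancy, such as anemia, hypertension, and chronic energy deficiency". It adds: "These changes were made before data analysis and have been documented in the protocol". No date is attached to the change.

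Under Randomization, Allocation, and Blinding it says: "Blinding was not possible both for the treatment provider (researcher) and for the sample". The Table 4 row on timing reads "Data analysis March 2025 June 2025". The abstract says that the data were analysed in April 2025.

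Under Data Analysis, pregnancy complications is a binary outcome in a mixed effects logistic model with a random intercept for the class cluster, tested two-sided at .05.

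**The concern.** Changing a primary outcome during a trial is defensible if those who decide cannot know how the change will affect the comparison. What matters is which data existed at that time and who could see them. Whether the formal analysis had been run is a weaker test, because in an open trial an impression of the results can form well before then.

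The new wording also does not settle the event. The model needs one yes/no value per woman, while the text gives three examples. A fourth condition could be counted, or not, without departing from what is written.

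At stake is whether a reported effect on complications can be credited to the intervention, or whether some of it may come from the choice of what to count.

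**Working it through.** **1. Does the timing assurance exclude knowledge of outcomes?** The dates come from the abstract, Population and Table 4 (whose dates are headed as planned and tentative).

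| Step | When |
|---|---|
| Recruitment, at 20 to 22 weeks' gestation | November 2023 to January 2024 |
| Intervention | February to July 2024 |
| Follow-up and data collection | August 2024 to February 2025 |
| Analysis | March to June 2025 (abstract: April 2025) |

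Assume delivery by 42 weeks. A woman enrolled at 20 weeks at the end of January 2024 then delivers at most 42 − 20 = 22 weeks later, in early July 2024. Table 2 schedules complications at months 1, 2 and 3, so this outcome is complete by about mid-2024. Some eight months remain before March 2025. A change at any point in that gap would count both as after the start and as before analysis, with every complication already recorded.

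Study Outcomes says that all results were measured after labor, which does not match Table 2. Either reading leaves the outcome complete well before analysis.

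**2. Who could see data as they came in?**

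- Intervention arm, Study Design: "The results of the examination at each meeting were entered into the REST" app.
- Intervention arm, Intervention section (text after Figure 3): "If an abnormal value is entered, the app automatically flags the entry and provides a visual alert". Blood pressure and hemoglobin are the examples given there.
- Research team, Data Management, for missing or inconsistent data: "follow-up verification was conducted by the research team through direct contact with the respective participants or midwives".
- Control arm, Data Management: paper forms transcribed to electronic format, at a time not stated.

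Live entry is thus documented for one arm. No section describes anyone looking at a comparison between arms.

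**3. Is the event fixed?** The three named conditions correspond to checks in the 10T examination (hemoglobin, blood pressure, mid-upper arm circumference). They are introduced as examples, so other maternal conditions are neither included nor excluded.

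**4. Hypothetical size.** The article gives no figure to reproduce on this point. Suppose that the choice lay between two definitions, that neither is affected by treatment, and that the more favourable was picked after both results by arm were known. With Z1 and Z2 standard bivariate normal with correlation ρ, the chance of a nominally significant result is

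P(|Z1| > 1.96 or |Z2| > 1.96) = 1 − P(|Z1| ≤ 1.96 and |Z2| ≤ 1.96).

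| Assumed ρ | Two-sided error |
|---|---|
| 0.5 | 9.1% |
| 0.7 | 8.3% |
| 0.8 | 7.8% |
| 0.9 | 7.0% |

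With three candidate definitions and ρ = 0.6, simulation gives 11.8%. If the definition was fixed without sight of results by arm, the error stays at 5%. Neither the number of candidates nor ρ is in the article.

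**The case against.** The authors disclosed the change, which many do not, and they say that it is documented in the protocol. The full protocol is not shown and may well hold the date, the reason, the thresholds and the persons who decided. An article commonly leaves such detail there, so its absence is not by itself a fault. That stands. What remains is the assurance that the article chose to print, which is too weak for an unblinded trial, and a definition that is open as worded.

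Four stronger readings are tempting, and the documents do not support them.

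- *The definition was chosen on the results.* Nothing shows that anyone saw a comparison between arms. That would need control-arm data too, and live entry is described only for the intervention arm.
- *The .05 level has been lost.* The 7% to 9% depends on a results-informed choice between two assumed definitions. It does not measure this trial's error.
- *Severe events are no longer counted.* The list is open and refers to conditions experienced by the mother, so severe maternal complications are not excluded. Delivery method and birth weight are separate primary outcomes.
- *Outcome data built up under view for over a year, to February 2025.* Complications are scheduled at months 1 to 3, and deliveries should have ended around mid-2024. February 2025 is only the end of the data-collection phase.

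**Conclusion.** The point holds as an unexcluded risk and not as demonstrated bias. A primary outcome was redefined after the start, without a date, and the stated assurance is compatible with a choice made once all outcomes had accrued. The open list leaves the content of the binary event to be settled after the data are seen. This rests on the article's own dates and blinding statement, plus the assumption of delivery by 42 weeks. The hypothetical error of 7% to 9% rests further on two candidate definitions, correlations of 0.9 to 0.5 and a choice informed by results by arm. If the sponsor can show that the definition was fixed without such knowledge, the concern about timing ends, and only the need to close the list remains.

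**What to change.** 1. Delete *such as* and fix the component list for the refined outcome.
2. Analyse pregnancy complications as originally recorded in the same mixed effects logistic model, and report it beside the refined outcome with each component shown separately. The article gives no operational form of the original term. Use the full protocol's form if there is one, and otherwise all recorded complications.
3. State the date of the change relative to the first outcome data, and what data those who decided could see, by arm. A pointer to a dated entry in the full protocol would do.
4. If the change followed outcome data by arm, or this cannot be excluded, label the refined definition post hoc.

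The cost is one extra model and a paragraph, with no new data. The drawback is that the headline may become less favourable or noisier under the broader outcome.

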## Methods

### Study Design

This research is an experimental study with a cluster randomized controlled trial (RCT) design. Cluster RCT is a research design that has multilevel characteristics. Generally, cluster RCT research uses 2 levels, the cluster or group level and the individual level. In this study, the class cluster will include pregnant women and participants of the ANC class. To minimize the risk of selection bias, we implemented the following strategies: (1) randomization at the cluster level was performed after cluster enrollment, and baseline characteristics of participants across the intervention and control groups will be carefully assessed and reported. The research design is described in Table 1.

**Table 1 table1:** Research design.

Group	Activity sequence 1			Activity sequence 2			Activity sequence 3			Activity sequence 4
	Observation	Intervention	Observation		Intervention	Observation		Intervention	Observation	
Control	O_0_^a^	X_0_^b^	O_1_^c^		X_0_	O_2_^d^		X_0_	O_3_^e^	
Intervention	O_0_	X_1_^f^	O_1_		X_2_^g^	O_2_		X_3_^h^	O_3_	

^a^O_0_: early identification in pregnant women in the first class of pregnant women.

^b^X_0_: standard intervention for routine antenatal classes without an app.

^c^O_1_: observations in the second class of pregnant women (trimester 2).

^d^O_2_: observations in the third class of pregnant women (trimester 3).

^e^O_3_: observation of childbirth and the newborn.

^f^X_1_: introduction of the REST (Risk Identification, Evaluation Counseling, Systematic Monitoring, Troubleshooting) mobile app for pregnancy monitoring for mothers and midwives using the 10Tpregnancy examination standard.

^g^X_2_: monitoring pregnant women after using the mobile app.

^h^X_3_: monitoring pregnant women using the mobile app and preparing for childbirth during the third trimester.

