### Population

The target population in this study was all pregnant women in Purworejo Regency. The affordable population was all pregnant women in 11 subdistricts. In total, 14 inpatient health centers were included, which included 22 clusters of ANC classes. Each cluster or class group comprised 10 pregnant women who met the inclusion criteria.

The inclusion criteria were as follows: pregnant women with a gestational age of 20-22 weeks (trimester 2), pregnant women who had a pregnancy examination at a health facility, mothers who planned to stay in the research area for at least the next 2 years, and mothers who were willing to participate in the research by signing an informed consent form.

The exclusion criteria were as follows: chronic diseases that require special pregnancy care, inability to give birth normally, and inability to operate an Android cellphone. The applicant was dropped if she moved outside the research area, could not be contacted after agreeing to provide informed consent, or decided to stop participating in the research.

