**Assessments**								
	Baseline clinical measurements	—	—	X	—	—	—	
	ANC visit	—	—	X	X	X	—	
	Pregnancy complications	—	—	X	X	X	—	
	Mode of delivery	—	—	—	—	—	X	
	Birth weight	—	—	—	—	—	X	

^a^SPIRIT: Standard Protocol Items: Recommendations for Interventional Trials.

^b^Applicable.

^c^Not applicable.

^d^REST: Risk Identification, Evaluation Counseling, Systematic Monitoring, Troubleshooting.

^e^Intervention group.

^f^ANC: antenatal care.

^g^Intervention and control groups.

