### Study Outcomes

All results were measured at the end of the study after participants from both the control and the treatment group had undergone labor. The success of the intervention was determined from the examination data input in the REST mobile app. Results were compared between the 2 groups. In addition, the effectiveness of the app was assessed using a questionnaire.

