### Data Analysis

Descriptive statistics were used to find out the basic characteristics of the entire study group. For bivariable analysis, the independent *t* test or Mann-Whitney U test, and the chi-square test or the Fisher precise test were applied for categorical results, adjusting for group design, if necessary.

Multivariable analysis was performed using mixed effects models to account for clustering at the level of the ANC class cluster. A mixed effects linear regression model was used for sustained outcomes, such as the number of ANC visits and birth weight. Mixed effects logistic regression models were used for binary outcomes, such as pregnancy complications and delivery methods. All models included random interception to account for variations between clusters and fixed effects for interventions, as well as potential confounding variables, including maternal age, education level, socioeconomic status, obstetric history, and nutritional status. Statistical significance was determined using a 2-headed *P* value of <.05.

For each primary and secondary outcome, we used an estimate of the effect size and its precision (95% CIs). Other analyses, including subgroup analysis and customized analysis, of study results were also carried out. Stata 14.0 was used to analyze the data.

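### The primary complications outcome claims prevention but does not separate conditions already present at the first class from those that arise later

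*Protocol article*

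**What the plan says.** Under Primary Outcomes, Pregnancy Complications, the article states that monitoring with the app can prevent complications. It then defines the outcome, as refined after the trial began, as "specific conditions of complications experienced by the mother during pregnancy, such as anemia, hypertension, and chronic energy deficiency". No sentence limits this to conditions that start after the first class.

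The entries that bear on timing are these:

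- **Population:** women enter at 20-22 weeks. Chronic diseases needing special pregnancy care are excluded. Anemia and chronic energy deficiency at entry are not named.
- **Study Design, text:** the 10T examination, which includes blood pressure, mid-upper arm circumference and hemoglobin, is done at each of the three class meetings, so also at the first.
- **Study Design, Table 1:** O0 is "early identification in pregnant women in the first class of pregnant women". It stands before X1, the introduction of the app.
- **Table 2:** one row reads "Baseline clinical measurements — — X" and another "Pregnancy complications — — X X X". Both therefore have a mark in Month 1. App installation and training stand in the enrollment column, and app use starts in Month 1.
- **Study Outcomes:** "All results were measured at the end of the study after participants from both the control and the treatment group had undergone labor".

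Under Data Analysis, the mixed effects logistic model for complications carries fixed effects for the intervention and for "potential confounding variables, including maternal age, education level, socioeconomic status, obstetric history, and nutritional status".

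**The concern.** A prevention claim needs an outcome that the intervention could still prevent. A woman who is anemic or has a low arm circumference at her first class has a complication during pregnancy whatever the app does later. If she counts as an event, she adds equally to the expected risk in both arms. The difference between arms then shrinks and the trial loses power on a primary outcome.

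Only 11 clusters are randomized to each arm, so the share affected at O0 may also differ between arms by chance. Hemoglobin and blood pressure at O0, which would identify prevalent anemia and hypertension, are not among the named covariates. Nutritional status is, but without a measure or a time point, although chronic energy deficiency is itself a nutritional condition and part of the outcome. A reader cannot tell whether this covariate corrects for baseline status, or overlaps with the event being modelled.

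**Working it through.** **1. The timing statements side by side.** Table 1 puts O0 before the app. Table 2 gives complications and baseline measurements the same Month 1 column, with app use in that month as well; monthly columns cannot show the order within a month. Study Outcomes places all measurement after labor, whereas Table 2 has no complications mark after Month 3. No rule says whether a finding at O0 is baseline, outcome or both. Followed as written, the definition and Table 2 make it both.

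**2. The plan's own figure.** From Sample Size: 1.96, 0.842, and proportions 0.92 and 0.72. The unpooled formula gives

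n = (1.96 + 0.842)² × (0.92×0.08 + 0.72×0.28) / 0.20² = 7.851 × 0.2752 / 0.04 = 54.0 per group.

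Design effect = 1 + 9×0.05 = 1.45, and 54 × 1.45 = 78.3, rounded up to 79. Both stated figures reproduce.

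**3. Dilution.** Assumptions, none of them stated in the article:

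- 0.92 and 0.72 are the complication-free proportions, so the risks are 0.08 and 0.28 among women free of complications at O0.
- A share b of both arms already has a condition at O0.
- The app cannot undo those cases.

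Then control risk = b + (1-b)×0.28, intervention risk = b + (1-b)×0.08, and the difference = 0.20×(1-b).

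Effective n = 79/1.45 = 54.5 per arm. Power = Φ(difference / √(variance sum / 54.5) − 1.96), where the variance sum is p(1-p) added over the two arms.

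| b | Control | Intervention | Difference | Power |
|---|---|---|---|---|
| 0 | 0.280 | 0.080 | 0.20 | 80% |
| 0.1 | 0.352 | 0.172 | 0.18 | 59% |
| 0.2 | 0.424 | 0.264 | 0.16 | 43% |
| 0.3 | 0.496 | 0.356 | 0.14 | 32% |
| 0.4 | 0.568 | 0.448 | 0.12 | 24% |

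A pooled-variance formula gives 78/57/42/31/24%. With all 110 women per arm analysed (effective n 110/1.45 = 75.9) it gives 90/72/55/41/31%. The pattern is the same.

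**4. Chance imbalance at O0.** Take b = 0.2, 79 per arm, and the same design effect for baseline status (an assumption). The standard deviation of the between-arm difference in b is √(2 × 0.2 × 0.8 × 1.45 / 79) = 0.077, or 7.7 points. One point of b moves the any-time risk by 0.72 points in the control arm (1 − 0.28) and 0.92 points in the intervention arm (1 − 0.08). An imbalance of 7.7 points therefore moves the estimated difference by 5.5 to 7.1 points, against a diluted effect of 16. Over repeated randomizations this is added variance, not systematic bias. In the one trial actually run, it goes uncorrected unless O0 status is in the model.

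**The case against.** The strongest reply is that no sentence says prevalent cases are counted. A reader might infer that they certainly are. The documents support this only as the natural reading of the definition together with Table 2, and Study Outcomes contradicts Table 2 on timing. The article also says the refined definition is documented in the protocol. An onset rule, a closed list in place of the open one, and diagnostic thresholds may stand there, and their absence from an article is not a fault in itself. The chronic-disease exclusion may remove some prevalent hypertension. All of this stands, and it limits the point to a failure to separate the two kinds of case.

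Three further inferences go too far:

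- **That baseline is taken after app use has begun.** Table 1 puts O0 before the app. The two tables leave the order unresolved.
- **That adjusting for nutritional status removes part of the effect.** Measured before the app, it is an ordinary prognostic covariate and would partly account for prevalent chronic energy deficiency. Harm arises only if it is measured after app exposure, or if one reading defines both covariate and outcome. The overlap does not extend to hypertension.
- **That the power figures are the trial's own.** The article does not say which of its four primary outcomes 0.92 and 0.72 describe, and it gives no b.

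The covariate list is also introduced as inclusive, so baseline hemoglobin and blood pressure are unnamed rather than ruled out.

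Finally, any-time occurrence may be a deliberate choice. The introduction speaks of checking for the presence of complications, and the app is also meant to help manage problems once found. But the outcome section claims prevention and the conclusions expect a reduction. An any-time count also does not measure resolution, so this does not remove the point.

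**Conclusion.** The point holds in this form: the outcome does not separate conditions present at the first class from new ones, and Table 2 scores complications in the same column as baseline. On the natural reading, prevalent anemia and chronic energy deficiency count as events.

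The firm result is the dilution factor (1-b), given that b is equal in both arms and that the app cannot undo prevalent cases. The fall in power from about 80% to between 59% and 24% is an illustration for b from 10% to 40%, resting on the assumed meaning of the planning proportions. Equal prevalence in both arms would weaken the contrast without favouring either arm; a chance imbalance could move the estimate either way. The concern about nutritional status is conditional on when and how it was measured. The matter is worth correcting because it touches a primary outcome and the correction is cheap.

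**What to change.** 1. State that O0 values are those of the first-class examination before the app is introduced, and reconcile Table 1, Table 2 and Study Outcomes on timing. If the order differed in the field, report what was done.
2. Analyse anemia, hypertension and chronic energy deficiency found after O0, counting for each woman only conditions absent at O0. Say where the window ends, since Table 2 schedules no complications assessment after Month 3.
3. Adjust for O0 hemoglobin, blood pressure and arm circumference, with the last as the defined measure of nutritional status.
4. Report the any-time definition alongside.
5. The abstract says data were analyzed in April 2025. If so, label the new-onset analysis post hoc.

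The cost is small, because these measurements belong to the first 10T examination. Availability in the control arm should be confirmed: Study Design exempts that group from recording examination results, while Data Management says its data were collected on forms. The downsides are that women with all three conditions at O0 leave this one analysis, and that the women remaining are at risk of different numbers of conditions. Showing each condition separately makes the latter visible.
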